## Abstract

**Background:** Parkinson’s disease (PD) is a neurodegenerative movement disease that includes non-motor symptoms such as cognitive impairment. Long-term mind-body exercise has been shown to improve cognitive ability in PD patients, but the methods of assessment and intervention were inconsistent across studies. Wuqinxi is a mind-body exercise that is easy to learn, has few physical and cognitive demands, and is recommended for PD patients. Dynamic functional connectivity (DFC) has been associated with cognitive alterations in PD patients, but no studies have yet explored the effects of Wuqinxi on this association. The current protocol is designed to measure the effects of long-term Wuqinxi intervention on cognition in PD patients, and explore the underlying neural mechanisms through DFC.

**Methods:** A long-term single-blind, randomized trial will be conducted. PD patients and age- and gender-matched HC will be recruited; PD patients will be randomly assigned to either Wuqinxi or balance groups, and HC will all receive health education. The Wuqinxi group will receive a 90-min session of Wuqinxi intervention three times a week for 24 weeks, while the balance group will receive balance exercise instruction on the same schedule. Primary outcomes will include assessment of cognitive domains and dynamic temporal characteristics of functional connectivity. Secondary outcomes will include severity of motor symptoms, mobility, balance, and emotional state. Assessments will be conducted at baseline, at the end of 24 weeks of intervention, and 12 weeks after interventions have ended.

**Discussion:** This study will provide evidence to the effects of Wuqinxi exercise on cognitive improvements in PD patients from the perspective of DFC, and will contribute to the understanding of neural mechanisms underlying cognitive enhancement through Wuqinxi practice.

**Clinical Trial Registration:**www.chictr.org.cn, identifier ChiCTR2000038517.

## Introduction

Parkinson’s disease (PD) is a neurodegenerative disease characterized by motor impairment as well as non-motor symptoms such as cognitive impairment (Kim et al., 2017; Fiorenzato et al., 2019). Previous studies have shown that PD patients have cognitive deficits in executive, attentional, speech and language, visuospatial, and memory domains (Goldman and Sieg, 2020). Most interventional studies have focused on improving motor ability because it is the classical symptom of PD. Cognitive impairment, however, has not been addressed as thoroughly, even though it not only reduces quality of life for the patient but also increases cost of care and caregiver burden (Pigott et al., 2015). Cognitive impairment can occur from early to advanced stages of PD. Longitudinal studies have shown that more than 25% of patients with mild cognitive impairment develop dementia within 3 years and up to 50% of patients with early PD develop cognitive decline within 5 years (Broeders et al., 2013; Pedersen et al., 2013). Thus, the clinical management of cognitive impairment is a long-term challenge, and there is an urgent need to develop evidence-based treatments for cognitive enhancement in PD patients.

No medications have yet been shown to slow PD progression, but there is substantial evidence for long-term exercise attenuating PD progression (Ahlskog, 2018). A cross-sectional, questionnaire-based study showed that regular exercise was associated with less cognitive decline after 1 year (Oguh et al., 2014). There is growing evidence that mind-body exercise can improve cognition, executive function, learning, memory, and verbal fluency (Zhang Y. et al., 2018; Wu et al., 2019; Zhang et al., 2021). However, the methods for intervention and assessment were inconsistent across studies, so it is difficult to draw conclusions about the mechanisms of mind-body exercise on cognition. In order to clarify the mechanisms, we should first focus on only one approach and use a variety of tools to track and assess the effectiveness of the intervention.

Previous studies have shown that mind-body exercise can improve the cognitive abilities of middle-aged and elderly people (Zou et al., 2019). Wuqinxi imitates the movement and breathing patterns of five animals (tigers, deer, bears, apes, and birds) and emphasizes the integration of body, breath, and mind (Guo et al., 2018). It is a kind of mind-body exercise which is easy to learn and has few physical and cognitive demands (Guo et al., 2018; Zou et al., 2019). Thus, PD patients with physical and cognitive impairments may choose Wuqinxi as a complement to medicine (Zhang et al., 2014). However, few studies have been conducted to find the neural mechanisms underlying the improvements (Zhang et al., 2021). Thus, this long-term study protocol focuses on Wuqinxi and uses dynamic functional connectivity (DFC) to detect the cognitive changes in PD patients.

Studies have shown that temporal variation in functional connectivity during scanning time reflected cognitive changes in PD patients (Kim et al., 2017; Fiorenzato et al., 2019). Functional connectivity analysis is based on temporal correlations between spatially remote neurophysiological events (Friston, 1994; Di and Biswal, 2015). In the past, researchers have typically computed static functional connectivity (SFC) with the assumption that it remains constant throughout the duration of the scan (Friston, 1994; Di and Biswal, 2015). In recent years, however, a large number of researchers realized that functional connectivity in fact varies periodically (Chang and Glover, 2010; Allen et al., 2014; Di and Biswal, 2015). Compared with DFC, time averaged SFC ignore the underlying temporal variations of functional connectivity which may provide additional information about brain function (Zhang C. et al., 2018). This offers yet another dimension upon which to evaluate disease states, and DFC has since been applied to depression (Kaiser et al., 2016), Alzheimer’s disease (Schumacher et al., 2019), and Parkinson’s disease (Kim et al., 2017; Fiorenzato et al., 2019). Specifically, DFC was found abnormal at the early stage in PD and correlated with disease progression, cognitive impairments (Kim et al., 2017; Cordes et al., 2018; Díez-Cirarda et al., 2018).

The aim of this study protocol is to explore the effects of Wuqinxi intervention for cognitive impairment in PD by DFC analysis. We hypothesize that Wuqinxi will change the temporal characteristics of DFC as well as the motor and cognitive impairments of PD patients.

## Methods

The current study is designed as a longitudinal, single-blind, randomized controlled trial. The study has been approved by the local research ethics committee.

### Design and Procedures

PD participants will be recruited through the local hospital’s exercise intervention group. To reduce potential expectation bias and confirm eligibility, a research assistant will make telephone contact with those referred by a neurologist and follow up with interested participants. Healthy controls (HC) will be recruited from the local communities through posters during the same recruitment period. Participants with PD will be randomly assigned to one of two groups: Wuqinxi or balance. The total intervention period will be 24 weeks. Primary and secondary outcomes will be assessed at baseline (prior to intervention), immediately following the end of the intervention period, and 12 weeks after the intervention has ended (see Figure 1). All PD participants will follow their regular medication scheme during the study period. This protocol has been approved by the Ethics Committee of Shanghai University of Sport (102772020RT107). All participants who meet the inclusion criteria will sign informed consent prior to the study.

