### Participants

#### Parkinson’s Disease Patients

##### Inclusion criteria

•Patients with PD diagnosed according to the UK Parkinson’s Disease Society Brain Bank diagnostic criteria.•Age 55–75 years old.•Hoehn and Yahr (H&Y) score of 1–3.•20≤ Montreal Cognitive Assessment (MoCA) score ≤25.•Ability to walk and exercise independently.

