##### Exclusion criteria

•Tai Chi or other exercise habits.•Other diseases that could interfere with conduct of the study protocol.•History of head injury.•Other significant psychiatric, neurological, or systemic comorbidity.•Magnetic Resonance Imaging (MRI) signal abnormalities (such as cerebral vascular lesions, white matter hyperintensities, and evidence of space-occupying lesions) or artifacts.•Severe cognitive, visual, or auditory impairment.•Depression or anxiety.•Deep brain stimulation.•MRI contraindications.•Alcohol or drug dependency or abuse.

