### Sample Size Calculation and Blinding

Sample size estimation was performed by G^∗^power V3.1 software (Franz Faul, Universitat Kiel, Germany). According to the analysis, at least 44 participants should be recruited (22 participants per group) in order to be able to perform two-factor repeated ANOVA (within-between interaction) with a middle effect size of 0.25 (Cohen, 1988), level of significance of 0.05, and power of 95% (Mayr et al., 2007). Since some participants may need to be dropped from the analysis due to excessive head motion during scanning, 40 participants will be recruited for each PD subgroup and 40 HC will be recruited. According to a similar studies published recently (Fiorenzato et al., 2019; Chen et al., 2021), this sample size should be adequate for replicating the previous effects in Fiorenzato’s study. In order to attract more participants, we will offer generous compensation and long-term health guidance. Every participant will be offered with an individual exercise plan when the whole study was completed. Randomization of PD patients will be done at the website www.random.org. Two researchers will be trained to assess the outcomes, and they will be blinded to group and will not participate in any interventions.

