### Resting-State and Structural MRI Acquisition and Preprocessing

Resting state functional MRI data and 3D high-dimension T1 image will be collected using a 3T Siemens Magnetom Prisma MRI scanner. PD patients will take medication during MRI scanning to minimize movement artifacts and reduce discomfort. All participants will be instructed to keep their eyes open and focus on a white “+” on black screen, letting their minds wander and trying not to fall asleep during the 10 min 6 s resting state functional MRI scan (gradient echo/fast gradient echo pulse sequence: repetition time = 2000 ms; echo time = 30 ms; flip angle = 80°; matrix size = 106 × 106; number of slices = 62; and voxel size = 2.0 × 2.0 × 2.0 mm^3^ with no gap; number of total volume = 304). During the structural scan participants will be instructed to sleep (repetition time = 3130 ms; echo time = 2.98 ms; flip angle = 4°; matrix size = 256 × 256; number of slice = 176; voxel size = 1.0 × 1.0 × 1.0 mm^3^).

Data preprocessing will be conducted using the SPM12 package implemented in MATLAB R2019a^1^. Prior to preprocessing (1) the first four scans will be deleted from the resting functional volume; (2) functional scans will be realigned to the first volume to correct for interscan head motion; (3) functional scans will be segmented into gray matter, white matter, and cerebrospinal fluid using the Tissue Probability Map template; and finally, and (4) normalized into standard Montreal Neurological Institute space using non-linear transformations and spatially smoothed with a Gaussian smoothing kernel of 6 mm. Participants with head motion greater than 1 mm will be removed from the study (Liao et al., 2014).

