### Outcome Measures

All measurements will be conducted before the intervention begins (baseline), immediately after the 24 weeks of intervention, and 12 weeks after the intervention.

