## Discussion

To date, little is understood about the neural mechanisms underlying the improvement of cognitive ability in PD patients after mind-body exercise. Previous studies suggested that mind-body exercise can enhance cognitive performance in PD patients (Zhang Y. et al., 2018; Wu et al., 2019; Zhang et al., 2021). Among the various types of mind-body exercises, Wuqinxi has often been recommended as a complement to medicine to treat cognitive impairment (Zhang et al., 2014). Thus, the present study proposes a longitudinal protocol for enhancing cognition in PD patients with Wuqinxi intervention.

Previous studies have shown that dynamic temporal properties can reflect cognitive alterations in PD patients (Kim et al., 2017; Fiorenzato et al., 2019). Two distinct connectivity ‘states’ have been observed in PD patients: one is more frequent and characterized by a predominance of within-network connections, while the other is less frequent and characterized by between-network connections (Fiorenzato et al., 2019). The dwell time and transitions between these two states was significantly correlated with various cognitive domains in PD patients, suggesting that analysis of these states may help to further our understanding of neural mechanisms of cognitive enhancement. DFC provides a method with which to explore the effects of Wuqinxi at the brain network level, complementing the traditional evidence that focuses more on behavioral performance and motor function (Reynolds et al., 2016).

There are a few shortcomings and in this protocol that have to be considered. First, we calculated the simple size following the principles of behavior science (Cohen, 1988), but it may still be small for neuroscience. Second, we cannot exclude that dopaminergic therapy will have some effect on functional connectivity (Berman et al., 2016). Third, the depression/anxiety of patients may will also have effect on functional connectivity (Yan et al., 2020; Wang C. et al., 2021). Further, it is difficult to guarantee that after randomization wuqinxin- and balance-group is strict matched for baseline cognition.

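### Baseline cognition is named as a balance risk, yet the described allocation and the between-arm models make no use of the screening MoCA score

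*Protocol article*

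**What the plan says.** All references are to the Protocol article.

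- **Allocation.** Design and Procedures: "Participants with PD will be randomly assigned to one of two groups: Wuqinxi or balance". The only description of method is in Sample Size Calculation and Blinding: "Randomization of PD patients will be done at the website www.random.org". No stratum, block or balancing factor is mentioned.
- **Acknowledged limitation.** The Discussion says that "it is difficult to guarantee that after randomization wuqinxin- and balance-group is strict matched for baseline cognition".
- **What is known before entry.** The inclusion criteria for patients with PD require "20≤ Montreal Cognitive Assessment (MoCA) score ≤25".
- **Role of that score afterwards.** Primary Outcome Assessment lists MoCA, together with the RBANS cognitive domains and the dynamic connectivity measures.
- **Between-arm analysis.** Under Application of DFC in Wuqinxi Intervention, the clinical and neuropsychological data go into a two-factor repeated ANOVA over three time points, with no covariate named. The connectivity analysis adjusts for education and dopaminergic dose only.
- **Timing of baseline.** Design and Procedures: "Primary and secondary outcomes will be assessed at baseline (prior to intervention), immediately following the end of the intervention period". The sentence continues to the 12-week follow-up and refers to Figure 1. Outcome Measures: "All measurements will be conducted before the intervention begins (baseline), immediately after the 24 weeks of intervention, and 12 weeks after the intervention". Both date baseline by the start of the intervention; neither mentions randomisation.

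**The concern.** The article treats imperfect balance in baseline cognition as something to be accepted. The trial already holds the information needed to control most of it: a MoCA score exists for each patient with PD before allocation, because eligibility depends on it. That same scale is then a primary outcome. As described, the score is used neither in the allocation nor in the between-arm models.

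With 40 patients per arm, a visible chance difference in starting cognition is quite possible. It would make a modest treatment difference harder to interpret. Patients who start lower also have more room to improve and regress more towards the mean. Adjusting for a prognostic baseline score would also usually recover some precision.

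**Working it through.** **1. The plan's own sample-size figure.** This point does not dispute it. For the within-between interaction, λ = f²·N·m/(1−ρ), df1 = (k−1)(m−1), df2 = (N−k)(m−1). The article gives f = 0.25, α = 0.05, power 95%, k = 2 arms and m = 3 time points; ρ = 0.5 and sphericity are not stated and are assumed. At N = 44: λ = 0.0625 × 44 × 3/0.5 = 16.5, df = 2 and 84, power 95.6%. At N = 42 power is 94.6%. The stated 44 is reproduced. Recruitment is set at 40 per PD arm.

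**2. Chance difference at baseline without stratification, in SD units.** The standard error of a standardised difference between two arms of n is √(2/n).

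- n = 40: √(2/40) = 0.224. The 95% range is ±1.96 × 0.224 = ±0.44 SD. The probability of a difference above 0.25 SD is 26%; above 0.3 SD it is 18%.
- n = 22, if losses took the arms down to the stated minimum: √(2/22) = 0.302. The 95% range is ±0.59 SD, and the probability of a difference above 0.25 SD is 41%.

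**3. The same in MoCA points.** The article gives no SD, so two assumptions are shown for n = 40.

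| Assumed MoCA distribution | SD | SE of difference | 95% range | P(difference > 0.5 point) |
|---|---|---|---|---|
| Uniform on 20 to 25 | √((6²−1)/12) = 1.71 | 1.71 × 0.224 = 0.38 | ±0.75 | 19% (18% by simulation) |
| More concentrated | 1.0 | 0.22 | ±0.44 | 2.5% |

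**4. Effect of stratifying.** Take two strata, 20–22 and 23–25, with uniform scores. Within a stratum of three equally likely scores the SD is √((3²−1)/12) = 0.82. With perfect balance between strata, the SE of the difference would be about 0.82 × 0.224 = 0.18 points. A simulation of 10,000 trials of 80 patients, with permuted blocks of 4 within strata, gave 0.19, slightly higher because last blocks may be incomplete. Fixed 40:40 allocation without strata gave 0.38. The probability of a difference above 0.5 point fell from about 18% to 0.7%.

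**5. Does a baseline difference pass straight into the treatment test?** No. Baseline is one of the three time points, and the sample size refers to the group-by-time interaction. A constant shift between the arms does not enter that interaction. What remains is regression to the mean and lost precision.

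**The case against.** The strongest reply is that this is a condensed article. It says where randomisation is done, not how, and strata or blocks may be set out in a fuller document. That stands in part: the absence of stratification is an inference. But the Discussion limitation makes it a strong one, because a sponsor who had stratified on cognition would be expected to say so at that point. The second reply is that chance imbalance under valid randomisation is not bias, that entry already confines MoCA to six values, and that baseline sits inside the repeated ANOVA. All of that is right, and it limits the point to precision and interpretability. The third is that other balancing schemes would also serve. That is also right; the cut-points used here are an example.

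Four stronger readings are tempting but not supported:

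- **That the sponsor admits an imbalance.** The Discussion says only that strict matching cannot be guaranteed, which is true of any randomised trial.
- **That baseline follows allocation, so patients are tested knowing their arm.** The order is unstated, not wrong. The wording is compatible with baseline before randomisation, and Figure 1, the study pipeline, is not shown.
- **That MRI eligibility exclusions fall after allocation.** The exclusion criteria include "Magnetic Resonance Imaging (MRI) signal abnormalities (such as cerebral vascular lesions, white matter hyperintensities, and evidence of space-occupying lesions) or artifacts", which points to a check before entry.
- **That the arms will miss 40:40 because each patient is allocated independently.** No text says so. A list drawn on the same website can be fixed at 40 per arm, and the article does state 40 for each PD subgroup.

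**Conclusion.** The point holds as a design improvement, not as a flaw that invalidates the comparison. The article names balance in baseline cognition as a weakness, holds the score that would largely control it, and describes no use of that score in allocation or between-arm analysis.

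The chance difference at 40 per arm has a 95% range of about ±0.44 SD. In points this is about ±0.75 if MoCA is uniform on 20 to 25, or ±0.44 if its SD is 1.0. Stratification into two MoCA bands halves the SD of the difference under the uniform assumption. The gain is in precision and credibility; no bias is removed.

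The conclusion rests on reading the allocation description together with the Discussion as meaning that cognition is not a stratum. The order of baseline and randomisation is a secondary matter of wording.

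**What to change.** - **Sample Size Calculation and Blinding:** replace the bare reference to the website with a pre-generated permuted-block list, stratified by screening MoCA (for example 20–22 and 23–25), with varying block sizes. It should be held by someone outside recruitment and outcome assessment.
- **Between-arm analyses under Application of DFC in Wuqinxi Intervention:** add the stratum or baseline cognition to the models. Because the test of interest is group by time, the stratum should enter with its interaction with time. Where MoCA itself is the response and baseline is one of its time points, use the stratum, or move baseline from the response to the covariates; the same value should not serve as both.
- **Secondary clarification, in Design and Procedures and Outcome Measures:** if Figure 1 does not already show it, state that baseline testing and the MRI lesion and artifact check are completed before randomisation.

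The cost is slightly more allocation administration and an extra model term, with no new tests or patients. The clarification has a limit: Resting-State and Structural MRI Acquisition and Preprocessing says "Participants with head motion greater than 1 mm will be removed from the study" without naming a visit, and fixing the order at baseline cannot prevent such removals at the 24-week and follow-up scans.

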**FIGURE 1 F1:**
[figure not shown]
Study pipeline.

A recently published protocol “Long-Term Wu Qin Xi Exercise on Response Inhibition and Cortical Connectivity in Parkinson’s Disease: Design and Implementation of a Randomized Controlled Clinical Trial” is similar to the current protocol (Wang Z. et al., 2021). Our protocol considers the whole brain and will use resting-state fMRI to detect the effects of Wuqinxi on PD patients, while the previously published one only take the primary motor cortex and response inhibition related brain regions (dorsal lateral prefrontal cortex, right inferior frontal gyrus, and presupplementary motor area) into consideration and use dual-site paired-pulse transcranial magnetic stimulation to evaluate the cortical connectivity.

We will first follow the methods in Fiorenzato and Kim’s researches to replicate the effects in their work (Kim et al., 2017; Fiorenzato et al., 2019), and then use DFC analysis as the main method to detect the effects of wuqinxin intervention in patients. In order to replicate the effects in Fiorenzato and Kim’s study, HC will be recruited and compared with whole PD patients before the intervention to support that DFC method could be used in our participants. HC will not be involved in the intervention procedure.

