#### Replication of the previous effects

##### Clinical and Neuropsychological Data Analysis

Statistical analyses will be performed using SPSS version 19.0. Demographic and clinical information of all PD patients will be compared using two-sample independent *t*-test (see Table 1). Pearson’s chi-square test will be used to compare categorical variables (see Table 1). Pearson’s correlation analyses will be applied between temporal properties and cognition (MoCA and cognitive performance in each domain) in whole PD patients as well as motor severity (UPDRS-III) before the intervention (see Table 2). The threshold for statistical significance will be set at *p* < 0.05.

**TABLE 2 T2:** Correlation between dynamic functional connectivity temporal properties and clinical characteristics (before intervention, after intervention, and follow-up).

		UPDRS-III	MoCA	Cognitive domains				
				I-M	V	L	A	D-M
Dwell time state I	*r*							
	*p*-Value							
Dwell time state II	*r*							
	*p*-Value							
Fractional windows	*r*							
	*p*-Value							
Number of transitions	*r*							
	*p*-Value							

*I-M = immediate memory; V = visuospatial; L = language; A = attention; D-M = delayed memory.*

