##### Group differences in dynamic connectivity: temporal and properties and strength

Group (whole PD patients vs. HC) differences in dwell time, fractional windows, and number of transitions will be examined using two-sample independent *t*-test analysis (*p* < 0.05, FDR correction, see Supplementary Table 1). Covariates will include education, levodopa and dopamine agonist equivalent daily doses. Subsequently, subject-specific medians corresponding to each group-level state will be estimated and two-sample independent *t*-test analysis will be used to compare the connectivity strength of each state at each unique regional pairing (*p* < 0.05, FDR correction) between groups (whole PD patients vs. HC), see Supplementary Table 1. Further, two-sample independent *t*-test analysis will be performed to compare strength abnormalities associated with cognitive deficits by comparing whole PD patients and HC (*p* < 0.05, FDR correction), see Supplementary Table 1.

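### The replication section tests 28 baseline correlations within PD patients at uncorrected p < 0.05, so an isolated significant one is weak evidence that the earlier effects recur

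*Protocol article*

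**What the plan says.** The text under Figure 1 in Design and Procedures sets an order: first reproduce the effects of two earlier DFC studies in PD, "then use DFC analysis as the main method to detect the effects of wuqinxin intervention in patients". Healthy controls are recruited for the first part and are to be "compared with whole PD patients before the intervention to support that DFC method could be used in our participants".

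The Statistical Analysis section, under Replication of the previous effects, has two parts:

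- **Clinical and Neuropsychological Data Analysis.** Pearson "correlation analyses will be applied between temporal properties and cognition (MoCA and cognitive performance in each domain) in whole PD patients", and also with motor severity (UPDRS-III), before the intervention. The significance threshold is p < 0.05 and no multiplicity correction is mentioned. Table 2 lists the measures. Its rows are dwell time in state I, dwell time in state II, fractional windows and number of transitions. Its columns are UPDRS-III, MoCA and five cognitive domains ("I-M = immediate memory; V = visuospatial; L = language; A = attention; D-M = delayed memory").
- **Group differences in dynamic connectivity.** PD-control "differences in dwell time, fractional windows, and number of transitions will be examined using two-sample independent" t-tests, followed by two sets of comparisons of connectivity strength. Each of the three sets is given FDR correction.

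Sample Size Calculation and Blinding plans 40 patients in each PD subgroup and 40 controls. It asserts that this is enough to reproduce the earlier effects, but names no target effect, size or power for that purpose.

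**The concern.** Two neighbouring parts of one section are held to different standards. The PD-control tests are corrected for multiplicity. The correlations, which are more numerous than the tests of temporal properties, are not. Both sit under a heading about replicating earlier effects, and the Discussion cites earlier correlations of dwell time and transitions with various cognitive domains as a reason for using DFC. A significant baseline correlation could therefore easily be reported as confirmation.

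The article does not say which correlations, or which signs, would match the earlier work. With 28 chances at the 5% level, some nominal significance is expected even if DFC is unrelated to cognition or motor severity in these patients. At stake is the wording of a supporting claim, that the earlier DFC effects were seen again in this sample.

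**Working it through.** **The plan's own figure.** The article gives no error rate or power for the replication step. Its one sample-size figure, 44 patients, belongs to the randomised comparison. It reproduces with f = 0.25, two groups, three timepoints and α = 0.05, assuming a correlation of 0.5 between repeated measures and no sphericity correction:

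- λ = f² × N × m / (1 − ρ) = 0.0625 × 44 × 3 / 0.5 = 16.5, on 2 and 84 degrees of freedom.
- Power is 95.6% at N = 44 and 94.6% at N = 42.

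So 44 is sound on those assumptions, but it says nothing about the correlations.

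**Number of tests.** Table 2 has 4 rows and 7 columns: 4 × 7 = 28 correlations per timepoint. Its title covers three occasions ("Correlation between dynamic functional connectivity temporal properties and clinical characteristics (before intervention, after intervention, and follow-up"), but only the baseline set belongs to the replication section.

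**If the 28 tests were independent and no association existed:**

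- Expected false positives: 28 × 0.05 = 1.4.
- P(at least one) = 1 − 0.95^28 = 76.2%.
- P(at least two) = 41.2%.

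**Allowing for dependence.** The measures within each set are related, so independence gives the upper end. Null data were simulated with 80 patients, 4 DFC variables, 7 clinical variables, no true association between the two sets, two-sided tests and 10,000 runs per setting. The within-set correlations are assumptions, because the article gives none. Among the clinical measures, the stated correlation holds between MoCA and the domains; UPDRS-III was set at −0.2 with each of them (0 in the first row).

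| Correlation within DFC / within clinical | P(at least one p < 0.05) | P(at least two) | P(at least one) if FDR is applied to the 28 |
|---|---|---|---|
| 0 / 0 | 75.7% | 41.0% | 5.0% |
| 0.3 / 0.3 | 69.3% | 37.5% | 4.8% |
| 0.5 / 0.3 | 65.2% | 36.1% | 4.7% |
| 0.5 / 0.5 | 60.0% | 33.8% | 4.3% |
| 0.7 / 0.5 | 53.4% | 31.3% | 4.1% |
| 0.8 / 0.6 | 44.8% | 28.1% | 3.6% |
| 0.9 / 0.7 | 34.9% | 24.0% | 3.3% |

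The mean number of false positives stays near 1.4 in every row (1.37 to 1.41); dependence only makes them cluster. At 0.5/0.5 the chance of at least one stays near 60% with 60 or 44 patients, so exclusions for head motion do not change the picture. With 80 patients, |r| = 0.22 already reaches p < 0.05.

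**After correction.** Bonferroni at 0.05/28 = 0.0018 gives 4.9% under independence. FDR (Benjamini-Hochberg) gives 3.3 to 5.0%, as in the last column.

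**The PD-control tests, for comparison.** Under a global null, each FDR-controlled family has about a 5% chance of any rejection. For the three families together this is 1 − 0.95³ = 14.3% if independent.

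**The case against.** The strongest reply is that the 28 correlations are not the test that the article relies on. The stated support for using DFC is the comparison of patients with controls. The correlations involve no controls, and every patient-control test is FDR-corrected. This stands, and it limits the point to the correlations. A reader might infer that the whole replication step can hardly fail. The documents do not support that: the chance of any false rejection among the patient-control tests is about 5% per family.

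Second, a reader might infer that any significant cell of Table 2 would count as replication. No such rule is written. In ordinary usage, reproducing a published effect means the same pair of measures with the same sign, and one named pair would meet that by chance only 2.5% of the time at two-sided p < 0.05. This also stands. What remains is that the article fixes the uncorrected threshold without naming the pairs or signs, so the looser reading is left open. The absence of a formal pass rule would on its own be detail that an article may leave to the full protocol.

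Third, a reader might infer that the randomised DFC result rests on this step. It does not. The text places one analysis after the other without a condition, and the randomised comparison has its own FDR correction. Its type I error is untouched.

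Fourth, with k = 2 states, the dwell times, fractional windows and transitions all summarise one two-state sequence, so strong dependence is plausible and 76% is too high as a single figure. This is fair; under the strongest dependence tried, the chance falls below one half. The expected count of 1.4 does not depend on it.

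**Conclusion.** The point holds in a limited form and is minor. Under the replication heading, 28 within-patient correlations are tested at uncorrected p < 0.05 beside patient-control tests that are corrected. With no true association, about 1.4 would be significant. The chance of at least one is 76% under independence and roughly 35 to 70% under the assumed within-set correlations. An isolated significant correlation should therefore not be read as replication.

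The figures assume two-sided tests, which the article does not state, and within-set correlations that it does not give. The finding does not extend to the validity of the patient-control comparisons or of the randomised DFC analysis.

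**What to change.** In the replication section:

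1. Apply FDR correction across the 28 baseline correlations, or label them exploratory and not evidence of replication.
2. Base any statement that the earlier effects were replicated on the PD-control differences in the temporal properties (dwell time in each state and number of transitions), with the same sign as in the cited study and FDR-adjusted p < 0.05.
3. State that, if these differences do not recur, this will be reported plainly.

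The cost is a few sentences, with no new data, visits or participants. The downside is that fewer correlations will be nominally significant, and replication may have to be reported as not achieved.
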